#### 7.1.2 Phase 1 – Pre-dose Assessment (Day-1 To Day 1)

The results from the screening visit evaluations will be reviewed to ensure the subject eligibility. The following procedures will be performed on Day -1 after check-in or the morning of Day 1 prior to dosing for all subjects:

- Reassessment of inclusion/exclusion criteria by review of all screening results and repeating any test if needed
- Physical examination, including body weight

- Vital signs, including temperature, pulse, respiratory rate and blood pressure
- Laboratory and pregnancy tests (tests performed in the screening period within 7 days of Day 1 do not need to be repeated on Day -1 or Day 1 unless clinically indicated). Pregnancy test is required for female subjects with childbearing potential
- [REDACTED]
- AE assessment
- Concomitant medication review

#### **7.1.3 Phase 1 - Treatment (Day 1 of Treatment Cycle 1)**

- ECOG performance status
- Vital signs
- 12-lead ECG
- [REDACTED]
- PK collection
- Study intervention
- Dispense study drug and instructions for dosing at home
- Dispense diary card
- AE assessment
- Concomitant medication review

#### **7.1.4 Phase 1 - Day 2 of Treatment Cycle 1**

- Vital signs
- PK collection
- Study intervention
- AE assessment
- Concomitant medication review

#### **7.1.5 Phase 1b (Day 8 of Treatment Cycle 1)**

- Laboratory assessments (including hematology, blood chemistry, urinalysis, coagulation etc.)

- Study intervention
- AE assessment
- Concomitant medication review

#### **7.1.6 Phase 1 - Day 14 of Cycle 1**

- Physical examination
- Vital signs
- Laboratory assessments (including hematology, blood chemistry, urinalysis, coagulation etc.)
- 12-lead ECG
- PK collection
- Study intervention
- AE assessment
- Concomitant medication review

#### **7.1.7 Phase 1 - Day 1 of Treatment Cycle $\geq 2$**

- Physical examination
- ECOG performance status
- Vital signs
- Laboratory assessments (including hematology, blood chemistry, urinalysis, coagulation etc.)
- Pregnancy test (serum or urine) is required for female subjects with childbearing potential in odd-numbered cycles.
- 12-lead ECG
- [REDACTED]
- [REDACTED]
- [REDACTED]
- PK collection
- Study intervention
- Dispense study drug and instructions for dosing at home

- Dispense diary card
- AE assessment
- Concomitant medication review
- Tumor assessment at the completion of treatment cycle 2 (assessment performed at the completion of every 2 treatment cycles for the first 8 treatment cycles and at the completion of every 3 treatment cycles thereafter until disease progression, start of new anticancer treatment, death, withdrawal of consent, or until end of study)

#### **7.1.8 Phase 1 - Upon Disease Progression or Unacceptable AE or Withdrawal from Study**

The following procedures will be performed unless otherwise specified:

- Physical examination
- Pregnancy test is required for female subjects with childbearing potential
- ECOG performance status
- Vital signs
- Laboratory assessments (including hematology, blood chemistry, urinalysis, coagulation etc.)
- 12-lead ECG
- [REDACTED]
- [REDACTED]
- [REDACTED]
- Tumor assessment
- AE assessment
- Concomitant medication review

#### **7.1.9 Phase 1 - Follow-Up**

- AE assessment
- Concomitant medication review
- Tumor assessment will be performed every 12 weeks for subjects who do not have disease progression on study. Assessments will be continued until disease progression, death, lost to follow-up, start of another anticancer therapy or other reasons that a follow-up is not possible.

### 7.2.2 Phase 2 - Screening Procedures (Day -28 To Day -1)

All subjects will be screened for eligibility and a repeat brief assessment, referred to below as the pre-dose assessment, will be conducted prior to the first dose of D-1553 to confirm eligibility. The following screening assessments must be performed within 28 days (unless otherwise noted) before enrollment:

- Written informed consent, must be obtained prior to undergoing any study procedure and may occur prior to the 28-day screening period
- Medical history review
- Diagnosis, history of solid tumor
- Demographics
- Physical examination, body weight and height
- Assessment against inclusion/exclusion criteria
- Pregnancy test which must be performed within 24 hours prior to initiation of first treatment. Pregnancy test is required for female subjects with childbearing potential.
- ECOG performance status
- Assessment of KRASG12C status
- Vital signs, including temperature, pulse, respiratory rate and blood pressure
- Laboratory assessment (including hematology, blood chemistry, urinalysis, coagulation, etc.)
- ECG (12-lead) performed in a recumbent position after 5 minutes of rest, collected in triplicate and read by central laboratory
- [REDACTED]
- LVEF measurement with Echocardiogram (only for Arm [REDACTED] F)
- [REDACTED]
- Tumor assessment (screening scans within 6 weeks prior to Day 1 of treatment cycle 1 are allowed, even if they are performed before the subject decides to join the study, to avoid radiation risk from extra scans)
- Concomitant medications

- [REDACTED]
- Archived tumor tissue (FFPE) for solid tumors
- Testing for HIV, Hep B and Hep C should be conducted during Screening for eligibility determination. A positive HBsAg will be considered positive for Hep B. A positive anti-HCV antibody and anti-HIV antibody will be considered positive for Hep C and HIV, respectively. [REDACTED]

### 7.2.3 Phase 2 – Pre-dose Assessment (Day -1 To Day 1)

The results from the screening visit evaluations will be reviewed to ensure the subject eligibility. The following procedures will be performed on Day -1 after check-in or the morning of Day 1 prior to dosing for all subjects:

- Reassessment of inclusion/exclusion criteria by review of all screening results and repeating any test if needed
- Physical examination, including body weight
- Vital signs, including temperature, pulse, respiratory rate and blood pressure
- Laboratory and pregnancy tests (these tests performed in the screening period within 7 days of Day 1 do not need to be repeated on Day -1 or Day 1 unless clinically indicated). Pregnancy test is required for female subjects with childbearing potential
- [REDACTED]
- AE assessment
- Concomitant medication review

### 7.2.4 Phase 2 -Treatment (Day 1 of Treatment Cycle 1)

- ECOG performance status
- Vital signs
- 12-lead ECG
- LVEF measurement with Echocardiogram (only for Arm [REDACTED] F)
- PK collection
- Study intervention
- Dispense study drug and instructions for dosing at home

- Dispense diary card
- AE assessment
- Concomitant medication review

#### **7.2.5 Phase 2 –Arms [REDACTED] F (Day 2 of Treatment Cycle 1)**

- Vital signs
- Study intervention
- AE assessment
- Concomitant medication review

#### **7.2.6 Phase 2 – Arms [REDACTED] F (Day 8 of Treatment Cycle 1)**

- Laboratory assessments (including hematology, blood chemistry, urinalysis, coagulation etc)
- Study intervention
- AE assessment
- Concomitant medication review

#### **7.2.7 Phase 2 - Day 1 of Treatment Cycle $\geq$ 2**

- Physical examination
- ECOG performance status
- Vital signs
- Laboratory assessments (including hematology, blood chemistry, urinalysis, coagulation etc.)
- Pregnancy test (serum or urine) is required for female subjects with childbearing potential in odd-numbered cycles.
- 12-lead ECG
- [REDACTED]
- LVEF measurement with Echocardiogram (only for Arm [REDACTED] F)
- [REDACTED]
- PK collection
- [REDACTED]

- Study intervention
- Dispense study drug and instructions for dosing at home
- Dispense diary card
- AE assessment
- Futility assessment (per arm according to Simon 2-stage design when stage 1 is completed for the respective arm)
- Concomitant medication review
- Tumor assessment at the completion of treatment cycle 2 (assessment performed every 2 treatment cycles for the first 8 treatment cycles and every 3 treatment cycles thereafter until disease progression, start of new anticancer treatment, death, withdrawal of consent, or until end of study.)

#### **7.2.8 Phase 2 - Upon Disease Progression or Unacceptable AE or Withdrawal from Study**

- Physical examination
- Pregnancy test is required for female subjects with childbearing potential
- ECOG performance status
- Vital signs
- Laboratory assessments (including hematology, chemistry, urinalysis, coagulation etc.)
- 12-lead ECG
- [REDACTED]
- [REDACTED]
- LVEF measurement with Echocardiogram (only for Arm [REDACTED] F)
- Tumor assessment
- AE assessment
- Concomitant medication review
- [REDACTED]

#### **7.2.9 Phase 2 - Follow-Up**

The following procedures will be performed for safety and efficacy (30 days after last dose) unless otherwise specified.

- AE assessment
- Concomitant medication review
- Tumor assessment will be performed every 12 weeks for subjects who do not have disease progression on study. Assessments will be continued until disease progression, death, lost to follow-up, start of another anticancer therapy or other reasons that a follow-up is not possible.
- Follow-up phone call every month to confirm OS

## **8 ADVERSE EVENT REPORTING**

### **8.1 Adverse events**

#### **8.1.1 Definition of Adverse Events**

An AE is any untoward medical occurrence in a study subject administered a product; the event need not necessarily have a causal relationship with the treatment or usage. An AE can therefore be any unfavorable and unintended sign (including an abnormal laboratory finding), symptom, or disease temporally associated with the use of an investigational product, whether or not considered related to the investigational product.

The time period for collecting AEs for each subject begins from the time the subject provides written informed consent, until the end of safety follow-up (30 calendar days after the last administration of investigational product or until the start of other anti-tumor therapy (see Section 8.2.4 for details).

Examples of AEs include but are not limited to:

- Aggravation of existing (prior to enrollment of study) medical conditions/ diseases (including exacerbation of symptoms, signs, laboratory abnormalities);
- Any new occurrence of AEs: any adverse medical conditions that newly occur (including symptoms, signs, newly diagnosed diseases);
- Abnormal laboratory test findings of clinical significance.

All AEs should be recorded in the AE page of the eCRF in details, including: event term, start and stop date, severity, seriousness, the causal relationship between the event and investigational drugs, actions taken with investigational product, as well as final results and outcomes.

#### **8.1.2 Severity Assessment of Adverse Events**

For severity of each AE, refer to the 5-grade scale developed from NCI-CTCAE v5.0. For AEs not included in NCI-CTCAE v5.0, the severity of each AE will be graded based on the general guidelines in Table 8-1.

**Table 8-1 National Cancer Institute Common Terminology Criteria for Adverse Events Severity Grading**

| Grade | Clinical Description of Severity                                                                                                                                                                                                                                                                       |
|-------|--------------------------------------------------------------------------------------------------------------------------------------------------------------------------------------------------------------------------------------------------------------------------------------------------------|
| 1     | Mild; asymptomatic or mild symptoms; clinical or diagnostic observations only; intervention not indicated.                                                                                                                                                                                             |
| 2     | Moderate; minimal, local or noninvasive intervention indicated; limiting age-appropriate instrumental ADL. Instrumental ADL refer to preparing meals, shopping for groceries or clothes, using the telephone, managing money, etc.                                                                     |
| 3     | Severe or medically significant but not immediately life-threatening; hospitalization or prolongation of hospitalization indicated; disabling; limiting self-care ADL. Self-care ADL refer to bathing, dressing and undressing, feeding self, using the toilet, taking medications, and not bedridden. |
| 4     | Life-threatening consequences; urgent intervention indicated.                                                                                                                                                                                                                                          |
| 5     | Death related to AE.                                                                                                                                                                                                                                                                                   |

Abbreviations: AE=adverse event, ADL=Activities of Daily Living.

### 8.1.3 Causality Assessment of Adverse Events

An investigator's causality assessment is the determination of whether there exists a reasonable possibility that investigational product caused or contributed to an AE, such as whether the occurrence of AE follows a reasonable temporal sequence from administration of investigational product, the properties of investigational product, toxicological and pharmacological effects of investigational product, the use of concomitant medications, subjects' underlying diseases, medical history, family history and dechallenge and rechallenge reactions, etc. Generally, the facts (evidence) or arguments to suggest a causal relationship should be provided.

The causality of AE with investigational product administration will be assessed as "related", "probably related", "possibly related", "unlikely related" and "not related".

## 8.2 Serious adverse events

### 8.2.1 Definition of Serious Adverse Events

An SAE is any untoward medical occurrence at any dose of investigational product that:

- Results in death;
- Is life-threatening (refers to an event in which the subject was immediately at risk of death at the time of the event, and it does not refer to an event which hypothetically might have caused death if it was more severe);
- Requires inpatient hospitalization or prolongation of existing hospitalization;
- Results in persistent or significant disability/incapacity;
- Results in congenital anomaly/birth defect;
- Other medically significant event.

Medical and scientific judgment is exercised in determining whether SAE is appropriate in other situations, such as important medical event may not be immediately life-threatening or result in death or hospitalization but may jeopardize the patient or may require intervention to prevent one

of the other outcomes listed in the definition above. These should also usually be considered serious. Examples of such events are intensive treatment in an emergency room or at home for allergic bronchospasm; blood dyscrasias or convulsions that do not result in hospitalization; or development of drug dependency or drug abuse.

### **8.2.2 Hospitalization**

Hospitalization is defined as any initial admission (even less than 24 hours) in a hospitalization, or any prolongation of an existing admission. Hospitalization does not include the following:

- Rehabilitation facilities;
- Nursing homes;
- General emergency admission;
- Same-day surgeries (as outpatient/same-day/ambulatory procedures)

Hospitalization or prolongation of hospitalization in the absence of a precipitating clinical AE is not in itself an SAE. Examples include:

- Admission for treatment of a preexisting condition not associated with the development of a new AE or with a worsening of the preexisting condition;
- Administrative admission (e.g., for yearly physical examination);
- Protocol-specified admission during a study (e.g., for a procedure required by the study protocol);
- Optional admission not associated with a precipitating clinical AE (e.g., for elective surgery);
- Preplanned treatments or surgical procedures. These should be noted in the baseline documentation for the entire protocol and/or for the individual subject;
- Admission exclusively for the administration of blood products.

Diagnostic or therapeutic noninvasive and invasive procedures, such as surgery, should not be reported as AEs. However, the medical condition for which the procedure was performed should be reported if it meets the definition of an AE. For example, an acute appendicitis that begins during the reporting period should be reported if the AE requirements are met, and the resulting appendectomy should be recorded as treatment of the AE.

### **8.2.3 Disease Progression and Death**

Disease progression (PD) is defined as that the disease under study is progressing or worsening, including radiological progression and progression of clinical symptoms and signs. New metastases relative to the primary tumor and the progression of the original metastases are both considered to be PD. Events that are life-threatening, requiring inpatient hospitalization or prolongation of existing hospitalization, resulting in persistent or significant disability/incapacity,

due to symptoms and signs of PD, should not be reported as an SAE. If there is any uncertainty about whether an SAE is caused by PD, it should be reported as an SAE.

In the study population of this trial, “disease progression” is an expected situation and shall not be documented as AE. When disease progression occurs, events used to confirm disease progression shall be reported as AEs. For example, in patients with epilepsy which are determined to be related to brain metastases, the AE term “epilepsy” rather than “disease progression” or “brain metastasis” shall be documented.

All cases of death that occur within 30 calendar days after the last administration of investigational product must be reported as SAEs, regardless of whether it is assessed by the investigator as likely due to disease progression, or the subject has received any other anti-tumor therapy. The term “death” should not be reported as an SAE term, but rather as an outcome of an event. The cause of death, medical conditions/disease (including exacerbation of symptoms, signs) should be used to be recorded in the eCRF and reported as SAEs. If the cause of death is unknown at the time of report, it should be recorded as “unknown cause of death”.

#### **8.2.4 Other Anti-Tumor Therapy**

If a subject begins any other anti-tumor therapy before the end of the safety follow-up period, only SAEs related to the investigational drug will be recorded after the start of such new anti-tumor therapies. Death during the safety follow-up period, regardless of whether the subject is receiving any other therapies, or whether the death is drug-related, must be reported in a timely manner.

#### **8.2.5 SAE reporting requirements**

The time period for collecting SAEs for each subject begins from the time the subject provides written informed consent, until [REDACTED] 30 calendar days after the last administration of other investigational product study treatment, whichever is earlier must be reported by the investigator.

All SAEs should be reported to InventisBio by the investigator on the “Serious Adverse Event or Adverse Event of Special Interest Report Form for Clinical Trial” (signed and dated) within 24 hours of awareness, regardless of whether this is an initial report or a follow-up report. The investigator should also report the SAEs to relevant organizations in a timely manner as required by local regulations.

The sponsor’s email to receive safety reports (for SAEs, AESIs or exposure during pregnancy) in this study:

Email: [[contact]](mailto:[contact])

SAEs occurring in a subject after the safety follow-up period has ended are reported to InventisBio if the investigator becomes aware of them; all SAEs that the investigator believes have at least a

reasonable possibility of being related to investigational product must be reported to InventisBio. The detailed record content of SAE should include symptoms, severity, causality with investigational product, time of onset, time of treatment, action taken with investigational product, follow-up time and method as well as outcome. If the investigator considers that a SAE is not related to investigational product while potentially related to the study conditions (e.g., termination of the original treatment or complications during the study), the relationship should be described in detail in the narrative section of SAE report form.

### **8.3 Adverse Event of Special Interest (AESI)**

#### **8.3.1 Overdose**

For this study, an overdose of D-1553 is defined as any dose over 50% of assigned dose; [REDACTED] For other combination [REDACTED] agents [REDACTED], an overdose is defined as any dose over 50% of assigned dose. All overdose should be reported to InventisBio by the investigator on “Serious Adverse Event or Adverse Event of Special Interest Report Form for Clinical Trial” (signed and dated) within 24 hours of awareness (see Section 8.2.5 for safety reports contact details).

Any clinical symptoms/signs or abnormal laboratory results due to overdose of any study therapy should be reported as an adverse event.

No specific information is available on the treatment of overdose of D-1553 [REDACTED]. In the event of overdose, the subject should be observed closely for signs of toxicity. Appropriate supportive treatment should be provided if clinically indicated.

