### **6.2.4 Administration**

In Phase 1a, each subject will receive daily oral doses of D-1553 (once -daily for Cohorts 1 to 4 and twice -daily for Cohorts 5 to 7) from Day 1 to Day 21 as one cycle on an empty stomach (no food and drink, except for water, for at least 0.5 hours before and after dosing) (Table 6-1). In Phase 1b, each subject will receive oral doses of D-1553 every day at recommended dose and schedule based on Phase 1a results in combination with other drugs. In Phase 2, each subject will receive oral doses of D-1553 every day at single agent RP2D or combination RP2D. All D-1553 doses should be taken on an empty stomach. On days when the subject is scheduled for a visit, D-1553 should be administered orally in the presence of the site personnel, especially when blood is collected for PK analysis. During the study, D-1553 should be taken at approximately the same time each day without treatment breaks until unacceptable toxicity, disease progression or withdrawal from the study. In the twice-daily schedule, D-1553 should be taken approximately 12 hours apart ( $\pm 3$  hours).

If a subject misses a dose, the dose will not be “made up” nor doubled at the next dose. If a subject vomits after taking a dose, the dose will not be “made up”, but the subject is to resume subsequent doses at the next day as prescribed.

Subjects will be instructed to swallow D-1553 tablets as a whole without chewing prior to swallowing. No tablet should be ingested if it is broken, cracked or otherwise not intact.

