**Table 6-1 Phase 1a (Dose Escalation)**

| Dose Levels | Dose Levels        | Tablets Required       |
|-------------|--------------------|------------------------|
| Cohort 1    | 150 mg once-daily  | 3 × 50 mg              |
| Cohort 2    | 300 mg once-daily  | 1 × 200 mg + 2 × 50 mg |
| Cohort 3    | 600 mg once-daily  | 3 × 200 mg             |
| Cohort 4    | 1200 mg once-daily | 6 × 200 mg             |
| Cohort 5    | 400 mg twice-daily | (2 × 200 mg) × 2       |
| Cohort 6    | 600 mg twice-daily | (3 × 200 mg) × 2       |
| Cohort 7    | 800 mg twice-daily | (4 × 200 mg) × 2       |

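### As worded, the overdose threshold in protocol section 8.3.1 is met by every correctly taken dose, so the 24-hour reporting rule cannot be applied as written

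*Protocol*

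**What the plan says.** Overdose is the first of the two AESI categories in protocol section 8.3. For the study drug, section 8.3.1 states that "an overdose of D-1553 is defined as any dose over 50% of assigned dose". After a redaction it turns to the other combination agents and gives the same definition, followed directly by the reporting duty: "an overdose is defined as any dose over 50% of assigned dose. All overdose should be reported to InventisBio by the investigator on" the form shared by serious adverse events and AESIs. The time limit is 24 hours from awareness. The section adds that no specific information exists on treating an overdose of D-1553.

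The doses to which this applies in Phase 1a are in Table 6-1: four once-daily cohorts (150, 300, 600 and 1200 mg) and three twice-daily cohorts (400, 600 and 800 mg per intake). Section 6.2.4 describes the twice-daily regimen: "In the twice-daily schedule, D-1553 should be taken approximately 12 hours apart".

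No other readable part of the protocol defines overdose or gives a limit above the assigned dose.

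**The concern.** The wording makes 50% a proportion of the assigned dose. A definition of overdose should separate excess intake from intended intake, and this one does not: the intended dose lies well above the stated limit. The same wording appears in both sentences, so a reader cannot correct one from the other.

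This is an operating rule, because it triggers expedited reporting. A site that wants to comply must replace the written threshold with one of its own. It must also decide whether to compare a single intake or the day's total, which matters for the twice-daily cohorts. Two careful sites could then treat the same event differently. Section 2.7 describes the study as first-in-human, and much of the dosing is self-administered at home (section 6.9), so consistent and prompt notice of excess intake has value.

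**Working it through.** The protocol gives no calculated figure to reproduce. The check is whether the assigned dose D satisfies the definition.

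**Inputs.** D for each cohort comes from Table 6-1, the 50% figure from section 8.3.1, and the twice-daily schedule from section 6.2.4.

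**Step 1, literal reading.** A dose is an overdose if it exceeds 0.5 × D. For comparison only, the table also shows one alternative reading, more than 50% above the assigned dose (exceeds 1.5 × D). That alternative is an assumption, used to show how far the readings differ.

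| Cohort | D per intake (mg) | 0.5 × D | D over it? | 1.5 × D | D over it? |
|---|---|---|---|---|---|
| 1, once daily | 150 | 75 | yes | 225 | no |
| 2, once daily | 300 | 150 | yes | 450 | no |
| 3, once daily | 600 | 300 | yes | 900 | no |
| 4, once daily | 1200 | 600 | yes | 1800 | no |
| 5, twice daily | 400 | 200 | yes | 600 | no |
| 6, twice daily | 600 | 300 | yes | 900 | no |
| 7, twice daily | 800 | 400 | yes | 1200 | no |

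The literal rule flags the assigned dose in 7 of 7 cohorts and the alternative in 0 of 7. The two limits differ threefold (1.5 ÷ 0.5 = 3).

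**Step 2, per intake or per day.** This keeps the assumed alternative and takes a subject assigned "600 mg twice-daily". The per-intake limit is 1.5 × 600 = 900 mg and the daily limit is 1.5 × (2 × 600) = 1800 mg.

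- One intake doubled, the other taken normally: the single intake is 2 × 600 = 1200 mg, which is over 900. The day's total is 1200 + 600 = 1800 mg, which is not over 1800.
- One intake missed and the next doubled, which section 6.2.4 forbids: the single intake is 1200 mg, which is over 900. The day's total is 0 + 1200 = 1200 mg, the assigned daily amount.

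Both events are overdoses per intake and neither is one per day. Doubling one intake gives the same split in Cohort 5 (800 over 600; 1200 not over 1200) and Cohort 7 (1600 over 1200; 2400 not over 2400). Once-daily cohorts show no such split, because intake and daily total coincide.

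**Step 3, could redacted text supply the answer?** The D-1553 definition is complete before the redaction that follows it, and the next readable sentence concerns other agents, so the hidden text probably concerns another product. A clarification for D-1553 cannot be ruled out. In the combination-agent sentence the redactions come before the definition, which ends in a full stop with the reporting duty straight after it. Redacted text is therefore unlikely to qualify that threshold.

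**The case against.** The strongest reply is that this is a drafting slip that nobody would apply literally. The word overdose and the instruction to watch for toxicity both point to excess intake. That is fair as a forecast of behaviour. It does not tell a site where the limit lies, and the repeated wording gives no help.

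A second reply is that excess intake is captured anyway. Section 6.9 requires diary review, tablet reconciliation and entry of dosing deviations in the case report form, and section 8.3.1 separately requires clinical or laboratory consequences of an overdose to be reported as adverse events. This stands, and it confines the exposure to the expedited notice.

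A third reply is that the phrase any dose already means a single intake, as section 6.2.4 uses the word for missed and doubled doses. The text does lean that way. Section 2.9, however, uses dose for a daily amount (1600 mg/day), so a confirming phrase is still useful. This is the weaker part of the point.

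A reader might also infer more than the documents support:

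- That sites will file a report for every tablet intake. The literal rule implies this, but it is not a credible prediction of conduct.
- That formally reduced doses would count as overdoses of the original dose. Section 6.2.7 refers to a subject's current assigned dose, so a reduced dose may simply become the new assigned dose.
- That AESI tables would be distorted. The readable safety analyses (section 9.4.4) do not name AESI counts.
- That the rule clashes with separate overdose wording for cetuximab. No such wording is readable.

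**Conclusion.** The point holds as an error in a safety-reporting definition. As worded, the threshold in section 8.3.1 includes the assigned dose in all 7 Phase 1a cohorts, and the same wording covers the other combination agents. It cannot be applied as written, and no other readable text corrects it.

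The likely effect is inconsistency between sites over which events receive 24-hour notice. Its frequency cannot be estimated from the protocol. The objective response rate, the dose-limiting toxicity evaluation and the sample size are untouched, and dosing deviations still reach the database.

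The conclusion on the literal wording needs only the readable text. Two further statements are judgements: that an excess above the assigned dose was probably intended, and that the redaction after the D-1553 clause probably concerns another product. The per-intake versus per-day contrast rests on the assumed reading of more than 50% above the assigned dose and applies to twice-daily dosing only.

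**What to change.** Correct both sentences in section 8.3.1, for D-1553 and for the other combination agents, and bring the AESI form instructions into line. Each should state whether the percentage is a proportion of the assigned dose or an excess above it, and confirm whether the comparison is per administration or per day under twice-daily dosing. If the redacted text already clarifies the D-1553 definition, the combination-agent sentence should be made to match. The limit itself is for the sponsor to set, and none is suggested here.

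The cost is about one sentence for each definition and a matching line on the form. No analysis, visit or sample size changes.
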